### Outcomes and measures

#### Primary outcome.

The primary outcomes will evaluate study feasibility (recruitment, retention, and survey completion across both arms) and intervention usability/acceptability. Feasibility will be assessed through enrollment rates (target ≥ 70%), retention rates (target ≥ 70%), and implementation feasibility using the Feasibility of Intervention Measure (FIM; target ≥ 80%) [50,51]. Acceptability will be measured with the Website Evaluation Questionnaire (WEQ), with success defined as ≥ 80% endorsement of top rating categories [52]. Usability will be assessed using the System Usability Scale (SUS), with a mean score ≥ 68 considered acceptable [53]. Technical performance will also be evaluated, including chatbot response accuracy (target F1 ≥ 0.7 [54]), response latency (<3 seconds), and differences across platforms (iOS vs. Android).In addition, caregiver comprehension will be assessed using the Patient Comprehension Questionnaire (PCQ), with success defined as a mean score ≥4.The PCQ will be administered to caregivers in the intervention arm at baseline and 3 months.

To further assess the DAPHNE chatbot, qualitative analysis will be completed for caregiver and provider interviews. This qualitative data will overlap with quantitative measures to gain a stronger understanding of provider and caregiver perspectives on feasibility, acceptability, and usability of the DAPHNE chatbot. For caregivers in the intervention group, qualitative interviews will be coded to evaluate factors that drive caregiver engagement with the DAPHNE chatbot and encourage use of the chatbot as well as barriers that may impact caregiver ability or want to use the chatbot. Interviews for caregivers in the control group will provide information about the current standard of care for caregivers with social needs and allow a comparison between resources or suggested resources caregivers receive in the current standard of care versus resources or suggested resources caregivers received while using the chatbot. Caregiver interviews across both groups will also be evaluated for caregiver perspectives toward study burden to determine the acceptability and feasibility of completing a larger scale trial of the DAPHNE chatbot. Clinician interviews will give first-hand insight into how well the DAPHNE chatbot could be integrated into clinic workflow by focusing on how useful the chatbot is perceived to be in a clinic setting, the challenges that may arise from using the chatbot in a clinic setting, and the ease with which the chatbot would be able to be integrated and possibly enhance the current standard of care.

#### Secondary outcomes.

Secondary outcomes address caregiver- and provider-level effects. Caregiver-reported outcomes (cPROMs) include stress [55], self-efficacy [56], satisfaction with access to community resources [57], and quality of life for caregiver and child as proxy [58]. These cPROMs will be completed by caregivers in both arms at baseline, 3, and 6 months. In addition to cPROMs, caregivers in both arms will complete the standardized HRSN screener. This survey will be administered at 3 and 6 months to capture changes in reported needs over time. Caregiver engagement with the chatbot is measured through system logs (e.g., minutes of use, number of logins, session durations, screenings completed, and resources accessed). Caregiver burden associated with study procedures will be measured in both arms using the Participant Burden Assessment (PeRBA; target ≥4) at 1, 3, and 6 months [59]. Provider perspectives on workflow integration will be assessed using the Workflow Integration Expectancy tool, with a target rating ≥ 4 [60]. These secondary outcomes will be analyzed to see how they change over the course of the trial and to eventually address whether there are any associations with outcome changes and chatbot use.

#### Exploratory outcomes.

Exploratory analyses will focus on healthcare utilization and economic outcomes to inform future large-scale trials. Electronic health record (EHR) data will be extracted to capture documentation of HRSN screening and referrals, adherence to well-child visits, missed appointments, emergency department utilization, and estimated healthcare costs. EHR data will be abstracted for all participants at 3- and 6-month follow-up period to capture pediatric primary care visits, social work referrals, and emergency department utilization. Billing and visit data will be used to estimate healthcare costs, including cost avoidance from reduced no-shows or ED visits. While the study is not powered to detect cost effects, descriptive comparisons between the DAPHNE and standard care arms will be conducted to identify patterns in service utilization and associated costs. Findings will inform the selection of economic outcomes and power calculations for a future NIH R01 trial. Additional exploratory outcomes will include continuous tracking of recruitment rates and dropout rates throughout the study period. Outcome measures, descriptions and planned timeline are also available at our registered protocol [61].

The details of study endpoints, including instruments, scoring rules, directionality, and primary timepoints are provided in Supporting Information (S1 Table).

### Sample size justification

This pilot trial is designed to estimate feasibility parameters rather than to test clinical efficacy. A prespecified feasibility benchmark is 6-month retention ≥70% (proportion of randomized caregivers completing the 6-month assessment). This target was selected because retention is a conservative, study-wide indicator of feasibility for a 6-month caregiver-facing digital intervention and provides guidance for assessing the viability and planning parameters of a future trial. Consistent with the ORBIT framework, this benchmark will inform, rather than solely determine, decisions regarding refinement of study procedures and progression to a larger efficacy study.

With n = 100 randomized caregivers, if retention is 70%, the corresponding 95% confidence interval (Wilson method) [62] will have an expected half-width of approximately ±9 percentage points, providing sufficient precision to inform decisions for a future trial.

For secondary outcomes, the intervention arm will allow estimation of mean SUS scores with acceptable precision. Assuming a standard deviation of approximately 12–15 points, the 95% confidence interval for the mean SUS will have an expected half-width of approximately ±3–6 points. Confidence intervals for proportions will be calculated using Wilson intervals, and confidence intervals for continuous outcomes will use t-based methods (or bootstrap methods if distributional assumptions are not met).

### Data analysis

Quantitative data (survey scores, engagement metrics, retention rates) will be summarized using descriptive statistics (e.g., mean, median, SD and IQR). Qualitative data will be transcribed and analyzed using thematic content analysis (hybrid inductive-deductive approach) in NVivo by two independent coders with ≥85% inter-rater reliability. Integration of quantitative and qualitative findings will follow a convergent mixed-methods design [63,64], in which both data streams are analyzed separately and then merged during interpretation. Integration will occur through joint display and narrative weaving, identifying points of convergence, divergence, and complementarity to refine the intervention and inform future trials.

### Longitudinal analysis of secondary outcomes

Continuous repeated outcomes (e.g., caregiver stress, self-efficacy, satisfaction with access to resources, and quality of life) will be analyzed using linear mixed-effects models with fixed effects for intervention arm, time (categorical), arm x time interaction, and baseline value of the outcome. A participant-level random intercept will account for within-subject correlation. Clinic site and baseline HRSN burden will be included as prespecified covariates.

Consistent with the ORBIT Phase IIb framework, these analyses are intended to examine directionality, consistency, and potential clinical relevance of change across study arms rather than to provide definitive estimates of treatment effect. Estimates with 95% confidence intervals will be reported descriptively. Interpretation will focus on patterns of improvement, variability, and the proportion of participants demonstrating meaningful change to inform whether progression to a fully powered efficacy trial is warranted.

Binary repeated outcomes will be analyzed using generalized linear mixed models with a logit link and participant-level random intercepts to account for within-subject correlation. The same prespecified covariates used in the continuous outcome models will be included. Results will be interpreted as exploratory indicators.

#### Missing data.

For longitudinal secondary and exploratory outcomes (e.g., stress, self-efficacy, satisfaction, quality of life), the mixed model will account for missing data that are missing at random. Covariates associated with missing data occurrence will be included in the models. Multiple imputation by chained equations [65] under a missing-at-random assumption will address missing baseline data and will also be applied as a sensitivity analysis to assess the robustness of results to alternative missing-data assumptions. The imputation model will include intervention arm, clinic site, baseline HRSN burden, baseline outcome values, time indicators, and prespecified predictors of missingness (e.g., demographic characteristics and prior engagement measures). Twenty or more imputed datasets will be generated, and parameter estimates will be pooled using Rubin’s rules. For feasibility-related process measures (e.g., survey completion rates), worst-case assumptions will be examined where appropriate to assess robustness of conclusions.

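### The sensitivity analysis meant to test other missing-data assumptions is multiple imputation under missing at random, the assumption the mixed model already makes

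*Protocol article*

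**What the plan says.** All the relevant text but one item is in the protocol article's Missing data section.

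- **Main analysis** of the longitudinal secondary and exploratory outcomes (stress, self-efficacy, satisfaction, quality of life): "the mixed model will account for missing data that are missing at random". The section adds: "Covariates associated with missing data occurrence will be included in the models".
- **Multiple imputation by chained equations**: "under a missing-at-random assumption will address missing baseline data". The same sentence, with the same subject, goes on to say that this imputation "will also be applied as a sensitivity analysis to assess the robustness of results to alternative missing-data assumptions".
- **Imputation model**: arm, clinic site, baseline HRSN burden, baseline outcome values, time indicators and "prespecified predictors of missingness (e.g., demographic characteristics and prior engagement measures").
- **Worst case**: "For feasibility-related process measures (e.g., survey completion rates), worst-case assumptions will be examined where appropriate".

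The amount of loss the plan can accept comes from Sample size justification: "A prespecified feasibility benchmark is 6-month retention ≥70" per cent, counted over all randomized caregivers.

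**The concern.** A sensitivity analysis for missing data is informative when it changes the assumption about the unseen values. Here the stated purpose is to try other assumptions, but the stated method keeps the one already in use. Both analyses take it that, given the variables in the model, caregivers who do not respond resemble those who do.

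Informative dropout is plausible on the article's own account. Data monitoring and risk management lists frustration with usability, privacy worries and inaccurate chatbot replies as risks. These arise from using DAPHNE, so they could drive loss in one arm more than in the other.

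If the two analyses agree, a report that follows this plan would call the results robust to assumptions that were never tried. The longitudinal analyses are read for direction and consistency, and the Longitudinal analysis section says they help judge whether a powered trial is warranted.

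**Working it through.** **1. The plan's own figure tied to dropout.** With n = 100, p = 0.70 and z = 1.96, the Wilson half-width is z/(1 + z²/n) × √(p(1−p)/n + z²/(4n²)) = (1.96/1.0384) × √(0.0021 + 0.000096) = 0.088. The interval is 60.4% to 78.1%, which matches the stated ±9 points. That figure is not in dispute. The benchmark is compatible with up to 30% missing at 6 months.

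**2. The assumptions side by side.**

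| Analysis | Outcomes | Assumption |
|---|---|---|
| Mixed model | Longitudinal secondary and exploratory | MAR |
| Multiple imputation | Same outcomes | "under a missing-at-random assumption" |
| Worst case | Feasibility process measures, where judged appropriate | Departs from MAR |

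No row gives a departure from MAR for the longitudinal outcomes.

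**3. Size of the error neither analysis would reveal.** Let m be the fraction missing in the DAPHNE arm and d the amount, in SD, by which non-responders there are worse than MAR predicts. A MAR analysis gives them a mean that is d too favourable, so the arm mean, and hence the arm difference, is too favourable by m × d. With the same problem in both arms the bias is m_D × d_D − m_C × d_C, which cancels if the arms are alike.

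The d values are assumptions. Taking m = 0.30 in the DAPHNE arm is also an assumption, because the benchmark is for both arms together.

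- d = 0.25: 0.30 × 0.25 = 0.075 SD
- d = 0.50: 0.30 × 0.50 = 0.15 SD
- d = 0.75: 0.30 × 0.75 = 0.225 SD

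**4. Direction.** The bias favours DAPHNE. A true null would look like a benefit of 0.075 to 0.225 SD, a true benefit would look larger, and a true harm smaller than the bias would look like a benefit.

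**5. Against sampling error.** With 35 completers per arm (70% of 50), the unadjusted standard error of an arm difference is √(2/35) = 0.24 SD, and the 95% half-width is 1.96 × 0.239 = 0.47 SD. If baseline adjustment uses an assumed correlation of 0.5, the standard error is 0.239 × √0.75 = 0.207 and the half-width 0.41 SD. The largest bias above, 0.225 SD, is about one standard error and about half the half-width.

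**6. Simulation.** Assumptions: 600 replicates, 50 per arm, baseline, 3 and 6 months, within-person correlation 0.5, true effect 0, higher score worse, and about 30% missing at 6 months. Imputation used arm, baseline and 3-month value, with 20 draws. Estimates are in SD; negative favours DAPHNE.

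| DAPHNE-arm dropout depends on | Mixed model | MAR imputation | Imputation with a 0.5 SD unfavourable shift in the DAPHNE arm |
|---|---|---|---|
| Observed 3-month value (MAR) | −0.01 | −0.01 | 0.14 |
| Unseen 6-month value | −0.20 | −0.21 | −0.05 |

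The first two methods correlated at 0.985 under both mechanisms. They agreed when both were nearly unbiased and when both were biased by about 0.2 SD, so agreement does not separate the two situations. The shift moved the estimate by about 0.16 SD in each row, in line with m × d at 31% to 32% missing.

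**The case against.** **The imputation model may be richer.** It names demographics and prior engagement, which the model in the Longitudinal analysis section does not. Engagement bears on who finds the chatbot unhelpful, so conditioning on it can make MAR more credible. This stands in part. The two analyses need not agree by construction, and the simulation left these variables out, so its 0.985 correlation does not describe the planned imputation model exactly. But the Missing data section also puts covariates linked to missingness into the mixed model. If engagement means chatbot logs, it does not exist for controls, who have no access. A wider conditioning set is still MAR.

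**No analysis of observed data can detect informative dropout.** True, and delta adjustment cannot either. The plan should not be faulted on that ground. The fault is that the analysis does not show how far results depend on the assumption.

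**There is a check outside MAR.** Correct. Study feasibility is a primary outcome, and its process measures get a worst-case check. A reader might infer that nothing in the plan departs from MAR, and the text does not support that. The gap is confined to the longitudinal secondary and exploratory outcomes.

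**The outcomes are exploratory and imprecise.** They are reported descriptively, and Future directions ties the next trial mainly to feasibility and acceptability benchmarks. With the unadjusted standard error of 0.24 SD, a true effect of 0.1 or 0.2 SD would show the wrong sign about 34% or 20% of the time with no informative dropout at all. This stands, and it limits severity.

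**Detail belongs in an analysis plan that is not shown.** That would answer a missing range or grid of shifts. It does not answer a sentence that fixes a method which cannot do what the sentence says.

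**Conclusion.** The point holds: for the longitudinal outcomes, the purpose and the method of the sensitivity analysis contradict each other within one sentence. Agreement between the mixed model and the imputation would support the modelling approach and choice of auxiliary variables under MAR, and nothing beyond that.

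Under the assumed 30% loss in the DAPHNE arm and shifts of 0.25 to 0.75 SD, the undisclosed bias is 0.075 to 0.225 SD in favour of DAPHNE. A reader might infer that informative dropout of this kind could turn a true benefit into an apparent harm. It could not, because the bias runs the other way. The risk is a false or exaggerated benefit, or a small harm that goes unseen.

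Severity is moderate: the outcomes are secondary or exploratory, the estimates are descriptive, and the bias lies inside the 95% half-width.

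**What to change.** 1. Keep MAR imputation for missing baseline data. Keep it also as a second analysis of follow-up data, described as a check on modelling approach and auxiliary variables under MAR.
2. For sensitivity to other assumptions, add delta-adjusted multiple imputation of follow-up values. Apply the shift in the DAPHNE arm, then in both arms, over a prespecified range in the unfavourable direction. Report how the estimate and its direction change. The 0.25 to 0.75 SD used here is illustrative; the sponsor should choose and justify the range before follow-up data are analysed.
3. If step 2 is not added, remove the claim that the imputation assesses robustness to other missing-data assumptions.

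The cost is a few lines of code on top of the imputation already planned, and sensitivity estimates that may be less favourable or wider. Step 3 costs only a change of wording; it cures the contradiction but leaves robustness to informative dropout unexamined.

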### Randomization and analysis population

The primary analytic approach will follow the intention-to-treat (ITT) principle, whereby all randomized participants are analyzed in their originally assigned group regardless of adherence or withdrawal. This approach preserves comparability between arms and reflects real-world implementation.

Because this pilot does not use stratified randomization, baseline characteristics (including clinic site and baseline HRSN burden) will be summarized descriptively by arm. If meaningful imbalances in baseline characteristics are observed by chance, we will maintain the original allocation and refrain from re-randomization or post-hoc modification. Instead, to enhance precision and reduce sensitivity to baseline differences, we will address any imbalance analytically using prespecified covariate adjustment in secondary and exploratory models. Adjusted models will include clinic (fixed effect), baseline HRSN burden (continuous or categorized as 1 vs ≥ 2), baseline value of the outcome when available, child age, and insurance type. We will report both unadjusted and adjusted estimates and interpret results as exploratory, focusing on directionality and consistency of findings (and, where applicable, the proportion demonstrating meaningful change) rather than statistical significance.

### Data monitoring and risk management

All study data will be collected through HIPAA-compliant electronic systems and stored on encrypted Nationwide Children’s Hospital servers. Data integrity will be ensured through automated validation checks, routine audits, and adherence to standardized abstraction protocols. Technical support will be available via a dedicated helpdesk during working hours, with all issues logged for iterative improvement.

Potential risks include participant frustration due to usability issues, privacy concerns, or inaccurate chatbot responses. To address these risks, the study incorporates caregiver training during onboarding, visual and video guides, and reassurance that DAPHNE complements rather than replaces clinical care. The chatbot’s performance will be continuously monitored for response accuracy and timeliness, with misinformation or errors flagged and corrected during weekly team reviews. Provider oversight will be integrated through periodic reporting of chatbot-identified needs and referrals to ensure appropriate follow-up. These strategies are designed to maintain caregiver trust, ensure accurate outputs, and safeguard participants throughout the study.

An independent Data Safety and Monitoring Board, consisting of 4 experts in primary care practices, AI/ML research, and biostatistics will oversee the trial to ensure participant safety, data integrity, and overall trial conduct. The board, which is independent of the study sponsor and funders, will meet semi-annually to review cumulative safety data, enrollment metrics, and protocol adherence. They will provide recommendations directly to the Principal Investigator and the managing institution regarding the continuation, modification, or termination of the study.

## Discussion

This protocol describes a pilot randomized controlled trial of DAPHNE, an AI-driven conversational agent designed to improve identification of health-related social needs and facilitate caregiver access to essential community resources. The study has potential to address the access barriers in pediatric primary care, where unmet HRSNs remain a major driver of adverse child health outcomes, yet routine screening and referral processes are underutilized [15–17].

By focusing on feasibility, acceptability, and usability, this study will generate critical data to guide refinement of both the intervention and the study protocol. Specifically, it will assess caregiver and provider engagement, evaluate technical performance across devices, and characterize barriers to study participation. Complementary analyses of provider surveys and EHR data will contextualize the current standard of care, providing essential information for selecting comparator conditions and outcomes in future clinical trials.

The results will directly inform a larger NIH R01 trial evaluating the efficacy and implementation of AI-driven HRSN screening. Consistent with the ORBIT model [32,33]. this study represents an intermediate phase (IIb) in behavioral intervention development, building the foundation for robust testing of clinical and operational outcomes. Longer-term directions include expansion to non-English-speaking populations, integration of voice interactivity, and cost-effectiveness analyses to assess healthcare savings from reduced no-shows and emergency utilization.

If successful, DAPHNE could advance personalized, equitable pediatric care by enabling real-time HRSN screening, reducing stigma in caregiver disclosures, and streamlining referral pathways. Beyond pediatrics, this approach has the potential to provide a generalizable framework for integrating AI-driven conversational tools into routine healthcare delivery and public health systems.

